### Randomisation

Eligible, consenting patients from the same study site who have completed baseline assessments will be randomised by a remote, centralised randomisation service (provided by York Trials Unit) in batches of 10–14 (intervention:control ratio of 1:1) using block randomisation in a single large block per batch. Following randomisation, a letter outlining the next steps will be sent to participants. For those allocated to the ACE arm, this will contain an invitation for them and their SO to attend five ACE sessions, including details of the venue, times and information.

### Blinding

By the nature of the interventions used within this study, blinding of the participants and facilitator is not possible. The research team responsible for data analysis and reporting will be blinded where possible.

### Intervention allocation

Consenting participants will be randomly allocated to either:*treatment-as-usual:* participants randomised to receive treatment-as-usual will continue to receive usual care delivered by their service.*ACE plus treatment-as-usual*: participants randomised to receive the ACE plus treatment-as-usual, will attend five 2 hours weekly sessions of the ACE programme, developed in Australia^48^ and will continue to receive usual care delivered by their service.

The ACE programme will be delivered as described in the published ACE manual^55^ by a trained facilitator to groups of hard of hearing people and SOs where possible. The same audiologist facilitator will deliver ACE to all groups.

ACE consists of six modules based on everyday communication activities known to be problematic for hard of hearing adults: module 1: communication needs analysis; module 2: conversation in background noise; module 3: conversation around the house; module 4: communication with difficult speakers; module 5: listening to other signals and module 6: listening to public-address systems.

Through the use of demonstrations, practical exercises, discussion and problem solving, participants and SOs will learn individual problem-solving skills which can be applied in a range of novel situations and discuss the use of communication strategies, lip reading skills, clarification skills and assistive technology.

### Intervention fidelity

Assessment of the fidelity to the ACE training of the audiologist facilitator and the delivery of the ACE programme will follow guidance from the NIH Behaviour Change Consortium,^56^ and conducted in a pragmatic approach mirroring the way fidelity of an educational programme, such as ACE, would be realistically assured in an NHS context. The trainers will reflect on the training sessions; fidelity of ACE delivery will be *facilitated* by supervision of the audiologist for the first session, with feedback and self-reflection used to address any issues; fidelity of ACE delivery will then be *assessed* via a self-monitoring form recording on a 1–4 scale (poor–good) of their adherence to the ACE manual for each module across all sessions.

### Intervention compliance

Measuring compliance is challenging in complex interventions such as this, where there are a number of interacting elements (such as the influences of the ACE facilitator, participants’ significant other, a varied selection of ACE module topics worked on and each individuals’ perceptions of their (or their SO’s) disability and treatment benefit). The intervention to be delivered is defined in the ACE manual^55^ and our understanding (measurement) of what is actually delivered will be informed by the fidelity measures above, weekly attendance logs and weekly session records. ACE participants and SOs will self-report goal setting for each module and the number of goals achieved during the programme, the number of completed exercises (homework) will be reported providing an additional measure of the level of engagement or compliance with the programme that is focused on the participant and their SOs.

### Concurrent treatments

Any additional treatments identified will be available to both arms when necessary (eg, hearing aid repairs, replacement batteries, etc). The bespoke resource use questionnaire (see below) will allow us to monitor additional treatment accessed during the study.

### Outcome measures

Figure 1 shows the main processes of the trial, their relationship with the outcome measures and their timing. Data will be collected at baseline (prior to randomisation); during all ACE sessions and after ACE session 5 for ACE participants and at an equivalent time for treatment-as-usual participants; and approximately 3 months post randomisation (6 months post hearing aid fitting).

The feasibility and the potential for a future large-scale study design (the study’s aim) will be measured by recording and evaluating:

#### ACE delivery outcomes

*Attendance*: Attendance rates of participants and SOs at ACE sessions will be measured and who attends ACE session with the participant will be recorded (objective 2).Fit of ACE with existing variations in service delivery models: comparison of attendance at ACE delivered at different study sites and their satellite clinics and the effect of using telephone or face-to-face follow-up appointments will be recorded (objectives 1 and 4).Can ACE be delivered as intended in the ACE protocol? This will be assessed through: (i) time taken to train the ACE facilitator successfully; (ii) number of ACE goals achieved by participants and (iii) facilitator’s adherence to the ACE protocol (fidelity) (objective 5).*Acceptability*: bespoke acceptability questionnaire regarding study processes, designed to explore participant and SO thoughts regarding the study including; ACE session organisation, session content, being approached and informed about the study and completing the questionnaires. The questionnaire is administered to participants and SOs at the final ACE session and at a comparable time for the questions for treatment-as-usual arm (objectives 3 and 4).

#### RCT delivery outcomes

*Recruitment*: number of follow-up cases in GP referred pathway; number of follow-up cases in GP referred pathway struggling with their hearing aid; number of and reasons for exclusions; number of patients who decline to participate and reason for declining; number who miss ACE intervention window (ie, unable to attend an ACE group within 1–3 weeks after randomisation); number given an appointment for an ACE group session and number of consented participants who fail to attend ACE sessions (objectives 6 and 7).*Allocation*: time taken to recruit and logistics of recruiting an optimally sized and located ACE group; time ACE started after randomisation (ACE intervention window); (objective 6).*PROM data*: completion of the outcome measures below at each time-point will be recorded as well International Outcomes Inventory fo Hearing Aids as extent of missing data within each outcome measure (objective 8).

#### Patient-reported outcome measures

*International Outcomes Inventory fo Hearing Aids* (*IOI-HA)*
52: a seven-item questionnaire designed to evaluate the effectiveness of hearing aid treatments. The domains covered are: daily use; benefit; residual activity limitations; satisfaction; residual participation restrictions; impact on others and quality of life. Responses are assigned a value from 1 to 5 and values summed. Higher scores indicate a more favourable outcome.*International Outcomes Inventory for Alternative Interventions (IOI-AI)*
57: a version of the IOI designed for use for non-hearing aid-based interventions such as ACE, covering the same domains as the IOI-HA.*Self-Assessment of Communication*
58: designed to measure the effect of hearing loss and hearing aid outcomes. This 10-item instrument covers questions about communication problems using a Likert scale ranging from 1 (‘almost never’) to 5 (‘practically always’). A percentage score is calculated by multiplying the raw score by 2, subtracting 20 and multiplying by 1.25.EQ-5D-5L^59 60^: a standardised generic instrument for describing and valuing health in terms of five dimensions (mobility, self-care, usual activities, pain/discomfort and anxiety/depression) using five levels of severity. Overall health on the day is also rated by the respondent on a 0–100 vertical visual analogue scale.*SF-36*
61: a generic health measure with 36 items assessing eight health concepts: physical functioning; role limitations due to physical problems; general health perceptions; vitality; social functioning; role limitations due to emotional problems; general mental health and health transition.

The following will be completed by participants’ SOs only:*IOI-AI: version for significant others*
56: a version of the IOI designed for use with SOs and non-hearing aid-based interventions covering the same seven domains as the IOI-HA.*IOI for hearing aids: version for SOs*
56: an extension of the IOI-HA for use with the SO covering the same seven domains as the IOI-HA.*Significant other scale for hearing disability*
16: a 27-item self-report tool, which assesses third-party disability in spouses of older people with hearing impairment. It measures the effects of hearing impairment on the SO in the following domains: changes to communication; communication burden; relationship changes; going out and socialising; emotional reactions to adaptations; concern for partner. It uses a 5-point response scale: 0=no problem to 4=a complete problem.

The feasibility of collecting postal questionnaire data at each time point will be evaluated. Table 1 shows the data collection schedule.

**Table 1 T1:** Data collection schedule Data are collected approximately 3 months posthearing aid fitting (baseline); at each ACE session 1–5 for the intervention arm and at a time equivalent to ACE week 5 for the treatment-as-usual arm; and approximately 6 months posthearing aid fitting

Study period	Recruitment	Allocation	Postallocation					
Time point	Baseline	0	ACE week 1	ACE week 2	ACE week 3	ACE week 4	ACE week 5	6 months
Recruitment								
Eligibility	•							
Informed consent	•							
Optional qualitative study consent	•							
Allocation		•						
Assessments								
Demographics	•							
IOI-HA	•						•	•
SAC	•							•
EQ-5D-5L	•							•
SF-36	•							•
Resource use	•							•
IOI-AI*							•	•
ACE participant attendance*			•	•	•	•	•	
ACE SO attendance~			•	•	•	•	•	
IOI-AI-SO*†							•	•
IOI-HA-SO†	•						•	•
SOS-HEAR†	•						•	•
Acceptability questionnaire							•	
Qualitative interviews (participant and SO)							•	
Qualitative interviews (audiologists)								•

*ACE arm only.

† Significant others only.

ACE, Active Communication Education; IOI-AI, International Outcomes Inventory for Alternative Interventions; IOI-HA, International Outcomes Inventory for Hearing Aids; IOI-HA-SO, IOI for hearing aids: version for SO; SAC, Self-Assessment of Communication; SF-36, Short-Form 36; SO, significant others; SOS-HEAR, Significant Other Scale for Hearing Disability.

### Screening and enrolment

Patients attending Audiology Clinics at YH and BRI will be approached to take part. Treatment-as-usual provided at the posthearing aid fitting follow-up will be according to site and therefore the recruitment process will vary slightly at each site:*York*: patients will be followed up via a telephone interview. Eligibility will be checked during telephone interview and from medical records. Details of eligible and interested patients will, with their permission, be passed onto a non-ACE researcher who will post out a patient information sheet (PIS) and conduct a telephone follow-up call a few days later to see if still interested. Contact information is provided in the PIS so that the patient has opportunity to ask questions regarding the study. If willing to participate, informed consent and baseline questionnaire will be completed by post. SOs of patients who are recruited at York will receive a SO-specific PIS, consent form and baseline questionnaire by post to be returned in a freepost envelope.*Bradford*: patients will be offered a face-to-face follow-up appointment 3 months post hearing aid fitting. Eligibility will be checked at this appointment and from medical records. Details of eligible and interested patients will be passed onto a non-ACE researcher who will provide a PIS and discuss the study. The patient will have the opportunity to ask questions and if willing, provide informed consent and complete a baseline questionnaire. If further consideration is required, the patient will be contacted by telephone call a few days later to see if still interested. In addition, if an SO attends the appointment with a patient, they will be provided with a SO-specific PIS, consent form and baseline questionnaire. Otherwise the documentation will be given to the patient to pass on to their SO or posted out.

We will monitor the proportion of patients referred to the treatment-as-usual pathway during the study recruitment who subsequently do not attend or are not contactable by telephone for their post-HA fitting follow-up in order to estimate how many referrals may potentially be lost to recruitment. We will liaise with audiologists to identify reasons for non-attendance where possible.

### Data collection and management

All data for the participant outcome measures will be collected by self-completed questionnaires returned by post or in secure boxes within the audiology clinics. Participants and SOs who fail to return their postal questionnaires will receive one reminder letter. Participants may also be asked to complete a questionnaire over the telephone, or asked to provide any missing data if required. Data from these paper forms will then be entered into a master database for the trial using either optical scanning techniques or entered manually.

Participants may withdraw from all or any aspects of the study without influencing their future care or treatment. A brief update of how the study is progressing will be sent out in order to maintain participant engagement with the study.

All information collected during the course of the trial will be kept strictly confidential. Information will be held securely on paper and electronically at York Trials Unit. All trial data will be identified using a unique trial identification number. Analytical datasets will not contain any identifiable information. Data will be archived for a period of at least 10 years following the end of the study.

### Statistical analysis

A single analysis will be conducted at the end of the trial using Stata V.13 or later. Data summaries and analyses will inform the design of a full-scale RCT of the intervention. Baseline data will be summarised by trial arm, using descriptive statistics for continuous data (mean, SD, median, minimum, maximum, number missing) and counts and percentages for categorical data. Recruitment rates will be reported monthly and overall, and by site. The flow of participants through the trial will be detailed in a Consolidated Standards of Reporting Trials flow diagram and referral, consent and attendance rates will be summarised overall and by site using counts, percentages and 95% CIs.

The number of ACE sessions attended will be summarised alongside any SOs who attended the sessions. Summaries will be provided overall, by site/clinic and by whether follow-up appointments were made as single or block booking. Acceptability data using Likert scales at 6 months, for participants, SOs and audiologists will be summarised separately using summary statistics and presented graphically using bar charts, by trial arm.

The number of participants withdrawing from the ACE intervention and/or the trial and any reasons for withdrawal will be summarised.

The time taken to train audiologists to deliver ACE and the number of ACE goals achieved by participants will be summarised. Fidelity scores (from self-monitoring forms) will be summarised overall and by session. The proportion of training and ACE intervention delivered as intended, as well as any adaptations to training/intervention will be reported. Variations in dose of ACE intervention will be measured through ACE attendance and attrition data.

Questionnaire return rates at each time point will be presented overall and by trial arm. PROMs at each time point will be summarised descriptively overall, by trial arm, and by ACE group for participants allocated to receive the ACE intervention. SD will be presented with 80% CIs to inform future sample size calculations. The proportion of participants at the floor and ceiling of each measure, at each time point, will be reported along with the standardised response mean (SRM) to measure the sensitivity of each questionnaire to detect change. The SRM will be calculated as mean change in scores or values divided by the SD in change scores.^62^ Questionnaire completion times (from self-report) will be summarised as a consideration for instruments going into the full-scale evaluation. Missing data will be reported as a proportion of the total expected data set for each measure and will inform feasibility.

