#### Trial delivery objectives

To assess RCT recruitment rates, evaluate the randomisation process and time to accrue ACE groups.To assess the acceptability of study processes to participants, SOs and audiologists (ie, those related to recruitment, the feasibility of identifying struggling hearing aid users, randomisation process, data collection, measurement of ACE fidelity and acceptability).To explore patient-reported outcome measures (PROMs) and estimate likely SD, including quality-of-life tools (EQ-5D-5L; Short-Form 36 (SF-36)) and a bespoke healthcare resource use/acceptability/utility questionnaire for use in an intended full-scale RCT.

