## Conclusion

This will be the first RCT of this type of group communication programme in the context of a public health service and as an adjunct to hearing aid fitting. The impact of this study will ultimately be realised by a larger fully powered RCT designed to determine the effectiveness of the ACE intervention in improving hearing aid benefit for hearing aid users within the NHS GP referral for a hearing aid pathway in the UK. The outcomes of this study will inform such a RCT.

The feasibility study will be deemed successful if:Seventy per cent of recruitment targets attained for all research components.Study consent/retention rates and proposed sample sizes, indicate delivery of the full RCT is plausible within a 5-year study period.Ninety per cent of ACE groups of five to seven consented participants formed within the intervention window with participants attending three of five sessions.Economic, acceptability, outcome measure and fidelity evaluation data successfully collecteParticipants, SOs and audiologists evaluate acceptability of the ACE and RCT positively.

(Measures with over 10% missing data maybe modified/replaced prior to the main trial).

The criteria for success will result in one of following outcomes:stop: full-scale RCT not be feasible in NHS setting;continue: feasible with modifications;continue: feasible with no modifications, close monitoring;continue feasible as is.

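### The plan ties only the raw SD of each outcome to the full trial's sample size; the baseline to 6-month correlation and a baseline-adjusted SD should be reported beside it

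*Protocol article*

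**What the plan says.** The third trial delivery objective begins "To explore patient-reported outcome measures (PROMs) and estimate likely SD". The Sample size calculation and recruitment section justifies the size of the feasibility trial by the precision of those SDs.

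The Statistical analysis section sets out how they will be reported. "PROMs at each time point will be summarised descriptively overall, by trial arm, and by ACE group" (the last for patients allocated to ACE), and "SD will be presented with 80% CIs to inform future sample size calculations". No summary of these measures by site is listed, and no correlation or model-based SD is named. The same section uses the SD of change for one purpose, the standardised response mean (SRM): "The SRM will be calculated as mean change in scores or values divided by the SD in change scores".

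Table 1 shows the IOI-HA, SAC, EQ-5D-5L and SF-36 at baseline and at 6 months, as are the IOI-HA-SO and SOS-HEAR for significant others. The IOI-AI and IOI-AI-SO have no baseline. On site, the Randomisation section says "Eligible, consenting patients from the same study site who have completed baseline assessments will be randomised", in batches allocated 1:1.

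The Conclusion lists among the success criteria: "Study consent/retention rates and proposed sample sizes, indicate delivery of the full RCT is plausible within a 5-year study period".

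**The concern.** When a trial measures its outcome at baseline and compares arms with adjustment for it, the variance that sets N is the residual variance after adjustment. The SD at a single time point is larger than the residual SD whenever baseline and follow-up are correlated. A feasibility trial that reports only the raw SD therefore hands its successor the less informative of two figures that the same data could supply.

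At stake is the quality of one input to the 5-year plausibility judgement. An N larger than the adjusted analysis needs makes the full trial look harder to deliver than it is.

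There is also a reason to estimate the correlation here and not import it. Entry is restricted on IOI-HA question 2, and that criterion was amended during the study. A correlation from unselected hearing-aid users may not carry over, at least for the IOI-HA.

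**Working it through.** **The plan's own figures.** The protocol states no N, effect size, power, SD or correlation for the full trial, so there is no full-trial figure to reproduce. For the feasibility trial, 6 groups x 7 patients x 2 arms = 84. This matches the Abstract; the sample size section says 88, which is a separate matter. I use 84 below.

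**Assumptions.** rho from 0.2 to 0.7; two-sided 5% level; 90% power; standardised effect d = 0.3 on the raw SD; 80% retention, so 0.80 x 84 = about 67 followed; group size 7; ICC of 0.05 or 0.10 among patients in one ACE group. None comes from the protocol except the group size, which is its stated maximum.

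**Step 1: effect of baseline adjustment on N.** Residual variance = (1 - rho^2) x raw variance, so an N from the raw SD is too large by 1/(1 - rho^2). For the example, n per arm = 2(1.960 + 1.282)^2(1 - rho^2)/0.3^2, rounded up and doubled.

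| rho | 1 - rho^2 | Excess from raw SD | Total N (raw SD: 468) |
|---|---|---|---|
| 0.2 | 0.96 | 4% | 450 |
| 0.3 | 0.91 | 10% | 426 |
| 0.5 | 0.75 | 33% | 352 |
| 0.7 | 0.51 | 96% | 240 |

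Dropout is not included.

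**Step 2: can rho be obtained from the planned output?** Largely, yes. rho = (SD0^2 + SD1^2 - SDchange^2)/(2 x SD0 x SD1). With SD0 = SD1 = 1, an SD of change of 1.183, 1.000 or 0.775 returns rho = 0.3, 0.5 or 0.7. The recovery is exact only if all three SDs come from the same patients. With dropout, the SDs at each time point may not, and the route gives no CI.

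**Step 3: how well would the trial estimate rho?** The lower 80% limit by Fisher's z is tanh(atanh(rho) - 1.282/sqrt(67 - 3)). Sizing on that limit reduces N by its square.

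| rho | Lower 80% limit | Saving at that limit | Saving if rho were known |
|---|---|---|---|
| 0.3 | 0.15 | 2% | 9% |
| 0.5 | 0.37 | 14% | 25% |
| 0.7 | 0.61 | 37% | 49% |

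**Step 4: the opposing effect.** ACE is delivered in groups, so outcomes in that arm may be clustered, which a raw SD also leaves out. With clustering in one arm, the average inflation is 1 + (7 - 1) x ICC/2, which is 1.15 at ICC 0.05 and 1.30 at ICC 0.10. Multiplying by 1 - rho^2 gives the N needed relative to the raw-SD N.

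| rho | ICC 0.05 | ICC 0.10 |
|---|---|---|
| 0.3 | 1.05 | 1.18 |
| 0.5 | 0.86 | 0.98 |
| 0.7 | 0.59 | 0.66 |

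At rho = 0.3 the unadjusted, unclustered N is slightly too small. At rho = 0.7 it is still much too large.

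**The case against.** The protocol says that the SDs will inform later calculations. It fixes no sizing formula, primary outcome or power. A reader might infer that the full trial is to be sized from raw SDs, but the text does not say so, and presenting an SD does not prevent a later calculation from adjusting for baseline. That stands.

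A reader might also infer that the baseline scores are ignored. They are not: the SRM requires the SD of change, from which rho can largely be recovered (step 2). What remains is that this quantity is planned as a measure of responsiveness, without a CI and without a stated common set of patients.

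The article is condensed and an analysis plan may exist. A table of correlations could properly sit there, so its absence from the article is not a fault in itself. The point is confined to what the article does name as the figure for sizing.

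The size of the excess is unknown. Restricting entry on an IOI-HA item tends to lower the correlation for that scale, which points to the end of the range where the gain is small. Clustering can remove it altogether. Both stand. Clustering is, however, a separate multiplier: once it is allowed for, the raw SD still overstates N by 1/(1 - rho^2), and two omissions that partly cancel are a poor basis for sizing.

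**Conclusion.** The point holds as a cheap improvement to a sizing input. It does not show an error that invalidates the plan. The SD is the only variance figure tied to the full trial's size. If that trial adjusts for baseline, an N from the raw SD alone is larger than needed by 4%, 10%, 33% and 96% at assumed rho of 0.2, 0.3, 0.5 and 0.7, before any clustering allowance. With 67 patients followed and a cautious lower limit for rho, the usable saving is about 2%, 14% and 37% at rho = 0.3, 0.5 and 0.7. Any gain from adjusting for site cannot be quantified from the document.

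Two further inferences are not supported. One is that the outcome measures would be ranked by raw SD. The protocol assesses them by floor and ceiling effects, SRM, completion time and missing data, and never by SD. The other is that a wrong decision to stop would follow. The criterion combines sample size with consent and retention, stands beside four others, sets no threshold for N, and leaves room to continue with modifications.

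**What to change.** In the Statistical analysis section, for each patient-reported measure with a baseline value, add two figures beside the raw SD, each with an 80% CI and each from the same paired patients:

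- the residual SD from a model of the 6-month score on baseline score, arm and site;
- the baseline to 6-month correlation.

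The IOI-AI and IOI-AI-SO have no baseline and keep the raw SD.

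In the success criteria in the Conclusion, state that the proposed sample sizes will use the adjusted SD with a conservative lower bound for rho and an allowance for clustering by ACE group, and show the raw-SD N beside them.

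The cost is one regression per measure and extra table columns, with no new patients, visits or data. The downside is small: rho is estimated imprecisely in a sample of this size (an 80% CI of about 0.37 to 0.61 at rho = 0.5 with 67 followed), which is why the lower bound is used.
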